### Randomisation and blinding

Participants will be randomly identified using a random number generator (SPSS) to intervention and control conditions. Permutation blocks of 36 will be used to ensure a minimum number of Let’s Talk and control group allocations.

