**Methods:**

A two arm parallel randomised controlled trial will be used with participants, who are being treated for their mental illness in adult mental health, non-government community mental health or family welfare services. The study will involve 192 parents, who are considered by their treating practitioner to be sufficiently well to provide informed consent and participate in an intervention (Let’s Talk about Children) or control group (treatment as usual). Participant randomisation will occur at the level of the treating practitioner and will be based on whether the randomised practitioner is trained in the intervention. Outcomes are compared at pre, post intervention and six-month follow-up. Recovery, parenting and family functioning, and quality of life questionnaires will be used to measure parent wellbeing and the economic benefits of the intervention.

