Following parent completion of the first questionnaire pack, the practitioner will be randomised to either the (1) wait list control group or (2) to receive training and deliver the Let’s Talk intervention. Randomisation has been designed to occur at the practitioner level to address any potential effects of attending Let’s Talk training in the control condition. The researchers will be blind to the allocation of the practitioner, with an independent administrative officer (based at a different site to the research team) allocating practitioners to groups based on the computer generated random sequence (using SPSS). Within 1 month after being allocated, Let’s Talk practitioners will be provided with training in the intervention. The control practitioners will continue treatment as usual and will not be trained in the intervention until completion of the study. Practitioners trained in the intervention will then offer Let’s Talk to their clients. Those parent-clients who decline the intervention will continue with treatment as usual with their practitioner (and continue in the research study if they wish as a separate comparison group in the analysis). Both wait-list control and Let’s Talk trained clinicians may refer any number of eligible parent-clients to the study who indicate interest in the research.

The control group will continue to receive ‘treatment as usual’ from their non-trained (in Let’s Talk) practitioner and will be informed about (and offered) Let’s Talk as they complete the final follow up questionnaire (following the training of their treating practitioner). Treatment as usual refers to the standard treatment or model of care usually provided to clients of each of the services involved in the trial. For the purposes of the trial this will be identified as treatment as usual in adult mental health clinical services, non-government mental health community support services and family support services.

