### Participant numbers

A total of 192 parents will be recruited. Participant numbers were initially determined by a power calculation indicating a minimum *n* = 54 participants with Crit F = 2.46 (using GPOWER 3.1, assuming 3 repetitions, a small effect size, an alpha of 5% and power of 95%) to be required. The larger number of participants will account for parent dropout and to allow between group comparisons across sectors (*n* = 32 per sector per group for both intervention and control groups).

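### The block of 36 has no defined unit, and as described the allocation does not secure the planned 32 parents per sector per arm

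*Protocol article*

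**What the plan says.** All places are in the protocol article.

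- **Randomisation and blinding** names participants as what is allocated: "Participants will be randomly identified using a random number generator (SPSS) to intervention and control conditions". It then gives the block size and its purpose: "Permutation blocks of 36 will be used to ensure a minimum number of" allocations to each arm.
- **Recruitment** names a different unit: "Randomisation has been designed to occur at the practitioner level". An independent officer at another site is responsible for "allocating practitioners to groups based on the computer generated random sequence". Practitioners in either arm "may refer any number of eligible parent-clients to the study".
- **Abstract, Methods** uses both terms at once: "Participant randomisation will occur at the level of the treating practitioner".
- **Participant numbers** sets the size: "A total of 192 parents will be recruited", broken down as "32 per sector per group for both intervention and control groups", so that groups can be compared across sectors.
- **Quantitative data analysis** makes arm and sector between-subjects factors. **Background** says that family-service parents generally have less severe illness but high comorbidity of family violence and substance use.

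No section mentions sector in connection with the allocation list.

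**The concern.** A list of parents in blocks of 36 and a list of practitioners in blocks of 36 are different designs. A reader cannot tell which was intended and so cannot reconstruct the list.

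A permuted block forces equal arms only when it is filled. Many trials that randomise practitioners recruit only a few dozen, so one block of 36 could be most or all of the list and could end part-filled. The stated purpose of the blocks, a minimum number in each arm, would then be only weakly met.

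The sample size also rests on equal numbers per sector and arm. Blocks that ignore sector control the overall arm totals but not the split within a sector. The sectors differ in severity and comorbidity, and sector comparisons are the stated reason for going beyond the minimum of 54. At stake is the precision of those comparisons.

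**Working it through.** **1. The plan's own figure.** 32 parents × 3 sectors × 2 arms = 192. This reproduces the total exactly, and each sector has 64 parents.

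**2. Fit of the block.** If the 36 counts parents, 192/36 = 5.33 blocks overall and 64/36 = 1.78 per sector. Neither is whole. The overall effect is trivial: 5 × 36 = 180, so 12 places of the last block are used, and the SD of the number allocated to one arm is √(12 × 0.25 × 24/35) = 1.43 parents.

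If the 36 counts practitioners, a single block (18:18) with n ≤ 36 places used guarantees only max(0, n − 18) in each arm:

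- n = 24: 24 − 18 = 6 practitioners.
- n = 18 or fewer: none.

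With 24 practitioners of 8 parents each, the SD of one arm's parent total around 96 is 8 × √(24 × 0.25 × 12/35) = 11.5.

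**3. Balance within sector, one case worked exactly.** Assume 36 practitioners, 12 per sector, in one complete block. The number of lists is C(36,18) = 9,075,135,300.

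- All three sectors 6:6: C(12,6)³/C(36,18) = 924³/9,075,135,300 = 0.087.
- At least one sector 8:4 or worse: 0.530.
- At least one sector 9:3 or worse: 0.175.

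**4. Range over the unknown number of practitioners.** This is a simulation of unstratified blocks of 36, with 64 parents per sector and equal caseloads. The numbers of practitioners are assumptions.

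| Units | Mean smallest cell (planned 32) | Some cell ≤ 24 | All six cells at 32 |
|---|---|---|---|
| 192 (parents as units) | 28.0 | about 5% | 0.4% |
| 96 practitioners | 26.1 | 31% | 0.9% |
| 48 practitioners | 23.4 | 71% | 1.8% |
| 36 practitioners | 23.3 | 52% | 8.7% |
| 24 practitioners | 19.1 | 97% | 3.5% |

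Unequal referrals widen this. With 48 practitioners and skewed caseloads, the smallest cell averages 19.6.

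**5. Cost in precision.** With equal caseloads, the information on the arm effect in a sector split a:b is ab/(a + b).

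- Sector-adjusted arm effect with splits 8:4, 6:6 and 4:8: balanced information 3 × 36/12 = 9; actual 32/12 + 36/12 + 32/12 = 8.33. The standard error rises by √(9/8.33) = 1.04, or 4%. Averaged over all lists in step 3 the rise is about 3%, with a 95th percentile of about 10%.
- Arm effect inside one sector: 8:4 gives √(36/32) = 1.06; 9:3 gives √(36/27) = 1.15.
- Parents at the averages in step 4: a 26:38 split gives √(1024/988) = 1.02; 19:45 gives √(1024/855) = 1.09.

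**6. What stratifying does.** Sector-stratified blocks of 4 give 32 in every cell in all the equal-caseload cases. With 48 skewed practitioners the smallest cell averages 23.1, better than 19.6 but still short. Stratifying while keeping blocks of 36 helps little when practitioners are few: with 24, the average is 18.8 against 19.1 unstratified.

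**The case against.** **The article is condensed and only silent on stratification.** This stands in part. A reader might infer that the list is unstratified, but no section says so, and a fuller protocol may name sector strata. What remains does not depend on silence alone. The article does state a unit, a block size and a purpose; the unit differs from the one in Recruitment, and the purpose leaves out the sector balance on which the sample size is built.

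**The unit is clear enough from the Abstract and Recruitment.** Largely true: practitioner allocation is the natural reading. It still does not settle what the 36 counts.

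**Thirty-two per cell is a recruitment number.** This stands. A reader might infer that the target cannot be reached by design. That is wrong: exact balance occurs in some lists, and because practitioners may refer any number of parents, thin cells can be topped up. The scheme does not secure the target, but it does not rule it out.

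**Sector is in the model.** This stands too. A reader might infer that chance imbalance confounds arm with sector. With sector as a factor, the consequence is some lost precision, small for the main arm contrast.

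**The practitioner numbers are invented.** They are assumptions, which is why a range is shown.

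**Conclusion.** The point holds as a fault in a stated method, of moderate weight. The unit that the block of 36 counts is undefined. If it is practitioners, the block is poorly matched to its purpose. With no sector stratum named, the scheme as described leaves balance of arms within sector to chance and does not secure 32 per cell.

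The size depends on an unknown number of practitioners. Across an assumed 24 to 96 with equal caseloads, the smallest cell averages about 19 to 26 parents; it is about 28 if parents are the unit, and lower with uneven referrals. The loss is in precision: a few per cent on the main arm contrast in the worked case, and more for effects within a sector and their comparison (6% at 8:4, 15% at 9:3). The figures do not show bias.

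**What to change.** Rewrite Randomisation and blinding along these lines: *Practitioners are the unit of randomisation. They are allocated 1:1, separately within each of the three service sectors, in permuted blocks of small, randomly varying size. The independent off-site officer holds the list. Parents take the allocation of their treating practitioner.* Remove the sentence that allocates participants.

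Keep sector as a factor in the analysis. In Participant numbers, describe 32 per sector per arm as a recruitment target, since unequal referrals will move parent counts even under stratified small blocks.

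The study began in 2013, so a new list can apply only to practitioners not yet randomised. For the others, report the method actually used: the unit, what the 36 counted, and whether sector was a stratum. If the existing list was already stratified, stating so removes that part of the point.

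The cost is a new list for the remaining practitioners, if any, and a paragraph of text. Small blocks make the next allocation slightly easier to guess; varying block sizes and off-site allocation limit this.

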### Data collection

Participants will complete measures prior to randomisation and 6 weeks post the completion of the Let’s Talk intervention (including an equivalent time frame for the control group) and 6 months after the post test. Participants will have the option to complete their questionnaires by hand (and post their questionnaire), verbally over the phone or in person with one of the members of the research team.

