### Outcome measures

The primary outcome measures included the *Parental Stress Scale* [13] that measures perceived parenting stress and includes 18 items that together measure total parenting stress along with four subscales of parental rewards, parental stressors, lack of control and parental satisfaction. The *General Functioning Index* of the *McMaster Family Assessment Device* [14] measures family functioning. The General Functioning Index consists of 12 items and measures an overall score of family functioning that distinguishes between ‘effective and problematic’ family functioning. The *SF-12v2 Health Survey* [15] will be used as a measure of quality of life. The survey is a 12 item quantitative instrument that records impacts of mental and physical health on daily activities. Outcomes were measured at 6 months followup.

The secondary outcome measures were the *Parenting Self-Agency Measure* [16] that assesses the general level of confidence parents have in their ability to engage in successful parenting behaviours. The measure examines the domains of confidence, helplessness in the face of child opposition, ability to resolve parent-child conflict, and effort in parenting and persistence. The *Recovery Assessment Scale* [17] is a 22-item recovery scale commonly used in mental health services. It includes five subscales as well as a total score: Personal confidence and hope; Willingness to ask for help; Goal and success orientation; Reliance on others; and No domination by symptoms. Each of the above measures has been widely used and are well validated and exhibit strong internal consistency.

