#### Economic evaluation

An economic evaluation will be conducted examining the costs of delivering the program (sourced from practitioner records) combined with costs for individuals of accessing treatment (using retrospective self-reported medication and hospital use along with patient and carer time away from usual duties). The evaluation takes a societal perspective including financial implications to the health system and individual patients and their carers. Outcomes will consist of the trial measures: impact on disease recovery rates and quality of life impacts (converting the SF-12 scores to SF-6D utility measures suitable for economic evaluation [18]. Incremental cost-effectiveness will involve the comparison between intervention and control groups of cost per additional person recovered and cost per quality adjusted life year gained using impacts from the SF-12. The cost-effectiveness model will take the form of a decision analysis modelling people between mentally ill and recovered health states, with results presented initially for 12 months follow up. Modelling to full life expectancy will be performed incorporating lifetime costs associated with mental illness sourced from the scientific literature. Extensive one-way and probabilistic sensitivity analyses will be conducted to assess the impact of uncertainty on results.

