**Table 1 Tab1:**
[figure not shown]
Overview of the research protocol for numbers to be enrolled, the intervention delivered, and measurement tools utilized throughout the study

t_1_ refers to the baseline measure, t_2_ is the post intervention or equivalent measure, and t_3_ is the 6 month follow-up measure post intervention

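### Post-test and follow-up are timed from completion of Let's Talk, so intervention parents who decline or stop get no assessment date under the stated rule, and the 6-month point is worded in two ways

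*Protocol article*

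**What the plan says.** All references are to the protocol article.

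- **Data collection** has a baseline before randomisation, a post-test "6 weeks post the completion of the Let’s Talk intervention", and then a last measure: "including an equivalent time frame for the control group) and 6 months after the post test".
- **The note to Table 1** says that t2 "is the post intervention or equivalent measure" and that t3 "is the 6 month follow-up measure post intervention".
- **Outcome measures** closes the paragraph on the primary outcomes with "Outcomes were measured at 6 months followup" and does not say from what date the 6 months run.
- **Recruitment** says that controls are told about and offered Let's Talk only "as they complete the final follow up questionnaire". On intervention parents who refuse, it says: "Those parent-clients who decline the intervention will continue with treatment as usual with their practitioner". They may stay in the study if they wish.
- **Quantitative data analysis** plans analyses of variance with time as a within-subjects factor and intends them to be by intention to treat.

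**The concern.** There are two issues, and the second matters more.

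First, the follow-up to which the primary outcomes are tied is described in two ways that, read literally, lie 6 weeks apart.

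Second, the clock for t2 and t3 starts at completion of the intervention. That event follows randomisation, its timing varies, and only intervention parents who finish ever reach it. An intention-to-treat analysis needs t2 and t3 from every randomised parent, including those who decline or stop, and the stated rule gives those parents no date. A within-subjects time factor also treats t1, t2 and t3 as the same occasions for everyone. If the occasions fall at different elapsed times in the two arms, change that would have occurred anyway under continuing usual care can be mixed into the arm contrast. If intervention parents who did not finish are assessed irregularly or not at all, the intervention arm becomes a selected group.

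**Working it through.** No sample size, alpha or power figure is involved. The check is calendar arithmetic, followed by setting the rule against each group of parents. One month is taken as 365.25 / 12 = 30.44 days.

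**1. The two wordings of t3, counted from completion**

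- Data collection: 6 weeks + 6 months = 42 + 182.6 = 224.6 days = 32.1 weeks = 7.4 months.
- Table 1 note, read literally: 6 months = 182.6 days = 26.1 weeks = 6.0 months.
- Difference: 224.6 − 182.6 = 42 days, which is 42 / 182.6 = 23% of the nominal 6 months.
- Interval from t2 to t3: 6.0 months under the first; 6.0 − 1.4 = 4.6 months under the second, if t2 stays at 6 weeks.

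**2. What the rule gives each group**

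| Group | Has a completion date before t3? | Date given by the article |
|---|---|---|
| Intervention, completed | Yes | t2 and t3 follow from completion |
| Intervention, declined | No | None; the equivalent period is stated for the control group only |
| Intervention, stopped part-way | No | None |
| Control | No; Let's Talk is offered only at the last questionnaire | An equivalent period, with no start date and no length |

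**3. Can the control interval be derived from the article?**

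It would have to match the time from allocation to completion in the intervention arm. Recruitment gives up to 1 month from allocation to the provision of training. An offer to the parent follows, and then two or three sessions (Background). No calendar length is given for the offer or the sessions, so the interval to be matched has no fixed length.

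**4. Illustration of the spread**

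Time from randomisation to completion is not stated. Assume it runs from 1 to 6 months. Time from randomisation to t3 is then:

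- Data collection wording: 1 + 7.4 = 8.4 months to 6 + 7.4 = 13.4 months.
- Table 1 note, literal: 1 + 6 = 7 months to 6 + 6 = 12 months.

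Either way, t3 spreads over 5 months among intervention parents who complete. This is spread within one arm. It becomes a difference between arms only if the controls' dates are not distributed in the same way, and the article gives no rule that would ensure this.

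**The case against.** **The two wordings may agree.** The Table 1 note uses post intervention as the label for the t2 wave, so its description of t3 may mean 6 months after t2, which is what Data collection says. Only Data collection sets out both intervals, and the body of the table cannot be seen. This stands: a reader might infer a firm contradiction, but the documents show only an ambiguity. It still needs settling, because the primary outcomes are tied to this time point.

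**Controls do have a rule.** The article intends an equivalent period for them. This also stands: a reader might infer that the arms will be assessed at different times since randomisation, but the text supports only a risk of that. An article may leave operational detail to the full protocol. The choice of completion as the anchor, however, is stated here, and the period to be matched is of no fixed length.

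**Silence on decliners is not exclusion.** Willing decliners stay in the research, so follow-up is evidently intended. That is true. The point is narrower: the stated rule does not produce a date for them, and its matching provision is worded for controls only.

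**Anchoring to completion is a recognisable choice.** It keeps t2 truly after the intervention, and a fixed window can put t2 before slow parents finish. That is a real trade-off, and it is a cost of the fix below.

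**The 12-month figure is not a third definition.** The Economic evaluation section speaks of a cost-effectiveness model "with results presented initially for 12 months follow up". A reader might count this as another conflicting follow-up time, but it can be the horizon of the model, and nothing here depends on it.

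**Conclusion.** The point holds as a weakness in how assessment times are fixed, with a secondary ambiguity of 6 weeks (7.4 against 6.0 months after completion) that rests on a literal reading of the Table 1 note. The firmer part is that intervention parents who decline or stop get no t2 or t3 date from the stated rule, and controls get a matched period with no start or length, while the analysis is intended to be by intention to treat. The consequence is a risk of unequal elapsed time and of selective loss or irregular timing in the intervention arm. A reader might go further and conclude that the arm contrast is biased. The article does not support that: it gives neither the time to completion nor the numbers declining or stopping, so neither the size nor the direction of any bias can be computed. The 5-month spread shown above rests on the assumed range of 1 to 6 months.

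**What to change.** 1. State one definition of t3, and reconcile Data collection, the Table 1 note and the 6-month statement under Outcome measures.
2. Schedule t2 and t3 at fixed times, with stated windows, from each parent's own baseline-questionnaire date. Apply this in both arms, whether or not Let's Talk is accepted or finished. Make the t2 window long enough to cover training and delivery.
3. Use the t3 window so defined for the primary analysis.

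The parent's own baseline date suits this purpose because every parent in both arms has one. The practitioner's randomisation date would be a poorer anchor: Recruitment allows trained practitioners to refer parents too, so some parents may enter after that date.

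The cost is wording and a scheduling rule, with no change to sample size, alpha or treatment. The drawback is that time since the last session will vary among intervention parents, and t2 may come before completion in slow cases. Both should be recorded and described.

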### Let’s talk practitioner training

Practitioners are trained in Let’s Talk by completing four online modules (1 h each) [12] followed by a 4 h face to face training session facilitated by experienced trainers within 4 weeks of completing the online modules.

